## Abstract

**Background::**

Kaposi sarcoma (KS) is the most common cancer among men in several Eastern African countries, yet treatment monitoring relies on imprecise, time-consuming ruler-based measurements defined by the AIDS Clinical Trial Group (ACTG). This method suffers from inter-observer variability, fails to capture lesion height or true geometric area, and performs poorly on dark skin. SkinScan3D (SS3D) is a portable, low-cost, AI-enabled 3D imaging device that provides objective measurements of KS skin lesion area, height, volume, and color. The Precision Imaging to Evaluate Kaposi Sarcoma (PRIME-KS) study evaluates whether SS3D provides more reproducible and accurate lesion measurements than the standard method, and validates its integration into routine clinical workflows in Kenya and Uganda.

**Methods::**

PRIME-KS is a multicountry prospective mixed-methods study with two clinical objectives. Objective 1 is a cross-sectional diagnostic accuracy study comparing SS3D with ruler-based measurement in 50 adults with KS (150 lesions) across sites in Kenya and Uganda. Two clinicians independently measure three lesions per participant using both methods. The primary outcomes are concordance correlation coefficient (CCC) for inter-rater reproducibility, and co-efficient of determination for accuracy. Objective 2 is a non-randomized before-and-after pilot study in 100 patients at three sites, evaluating device usability, acceptability, appropriateness, and feasibility using validated instruments, along with time-and-motion studies and activity-based micro-costing. Prior to these clinical objectives, a formative study used focus group discussions, discrete choice experiments, and human-centered design workshops to refine the SS3D device and protocols with end-user input.

**Discussion::**

PRIME-KS will provide the first rigorous evaluation of a 3D imaging device for monitoring KS treatment response in routine clinical settings. If SS3D demonstrates superior reproducibility and clinical utility, it could reduce unnecessary chemotherapy exposure and associated toxicities by enabling earlier, more objective assessment of treatment response.

**Structured summary {1b}:**

**Protocol version {2}:**

Version 1.2, 2 May 2026.

## Introduction

### Background and rationale {9a}

Traditional monitoring of treatment response for Kaposi sarcoma (KS) relies upon user observation and measurement of changes in lesion dimensions based on user observation of color contrast between lesion and normal skin. This may miss subtle changes in lesion pigment that may not be readily apparent, especially in patients with skin of color. In addition, this method suffers from inter-observer variability. Three-dimensional (3D) imaging removes user subjectivity and mitigates problems with identifying and characterizing KS lesion changes on patients by providing an independent measurement of cutaneous tumor volume based on 3D shape with precise calculation of lesion area, instead of the more problematic color contrast and perpendicular lengths.

There is an unmet need to develop simple, accurate, and less burdensome tools for monitoring KS treatment. Currently, response to KS treatment is assessed using manual ruler-based measurements defined by the AIDS Clinical Trial Group (ACTG) Oncology Committee. ^1, 2^ This method involves time-consuming and tedious manual measurement of multiple lesions using a ruler with millimeter precision, leading to inter- and intra-observer variation and failing to capture the true geometric area (Figure 1).

The color and degree of nodularity (including lesion height) of KS lesions are difficult to experimentally quantify and are not incorporated into the ACTG method, yet they often provide the most important information in assessing treatment response. ^2^ In settings with high prevalence of KS, the limited number of practitioners trained in evaluating KS treatment response exacerbates the problem. Due to the rigorous training required for competency in this method, it is only readily applicable in highly controlled clinical trial settings. The complex and onerous requirements (e.g. identify bidimensionally measurable KS cutaneous marker lesions, yet lesions appear in multiple shapes and sizes) make it impractical for routine care settings, resulting in possible inaccurate, unreproducible, and suboptimal treatment monitoring. Precise monitoring of KS treatment is essential to facilitate timely treatment adjustments. Treating clinicians primarily rely on subjective observation of treatment response and many err on the side of prolonging treatment with chemotherapy. Introducing a simple and user-friendly device could alleviate the need for extensive training and facilitate its adoption in routine care settings.

The current ACTG criteria primarily rely on reduction in bidimensional tumor size, which is not ideal for the majority of patients who present late with nodular lesions,^3^ that may not exhibit a significant change in bidimensional size. Instead, treatment response in these cases is characterized by a transition from a raised to a flat state and also accompanied by change in color from darker to lighter lesions. This response often precedes absolute reduction in bidimensional lesion size, leading to the unnecessary continuation of cytotoxic chemotherapy and the accumulation of associated toxicities. 3D imaging of lesions could introduce more precise treatment monitoring that is attuned to actual treatment response by detecting these early changes and facilitating early discontinuation of chemotherapy when indicated.

The SkinScan3D (SS3D) imaging device is a hand-held technology capable of measuring KS lesion height, area, and color, crucial determinants of treatment response for nodular lesions.^4^ It is a simple, low-cost, and user-friendly technology that combines liquid lens technology and artificial intelligence (AI), providing high-resolution 3D images/maps of KS skin lesions incorporating lesion height, area, and volume. We will explore the importance of measuring lesion height to obtain previously unmeasured unique clinical properties that may be used to objectively measure efficacy of treatment. We will also explore how changes in lesion color correlate with response assessment. The lack of an effective measurement tool is problematic because, while progress has been made in the last decade in the treatment of KS in Africa and elsewhere, ^5-8^ treatment is not curative and needs simple, reproducible methods to accurately, quantitatively, and reproducibly gauge the response to new treatment modalities.

Various alternative technologies, such as infrared thermal imaging, multi-spectral imaging, ultrasound, radiography, CT, MRI, PET, scintigraphy, and LDI, offer potential for improving tumor measurement. ^9^ However, none of these options provide a practical or affordable solution for clinicians to obtain accurate and reproducible 3D images or maps of cutaneous KS tumors, enabling serial comparisons crucial for assessing treatment response. The pressing clinical need to develop an improved, affordable, simple, accurate, and reproducible tool for monitoring KS treatment response is particularly urgent in East Africa, where KS ranks among the most prevalent cancers.^10^

We propose to evaluate SS3D and its potential contribution in the care of patients with KS by optimizing performance and integrating it into workflows at cancer treatment clinics in Kenya and Uganda. First, we will work with stakeholders to formally refine the technology to make it user-friendly and easy to integrate into clinical workflows. Second, we will compare lesion measurement using SS3D versus the standard manual method. Finally, we will assess SS3D’s contribution to improved clinical outcomes in real-world clinical practice.

### Explanation for the choice of comparator {9b}

The comparator is the current standard of care for KS lesion measurement: manual ruler-based assessment using ACTG criteria, which calculates lesion area as the product of the longest perpendicular diameters (Figure 1).^1, 2^ This method was selected because it is the globally recognized standard for KS treatment response assessment used in clinical trials. Comparing SS3D against this established method will determine whether SS3D offers superior reproducibility and accuracy for clinical decision-making.

### Objectives {10}

**Objective 1:** Compare reproducibility and accuracy of KS lesion size measurements between SkinScan3D and current standard of care measurement.

**Objective 2:** Validate and optimize SkinScan3D clinical workflow in real-world settings.

## Methods: Patient and public involvement, and trial design

### Patient and public involvement {11}

Patient and public involvement is central to PRIME-KS and was formalized through a dedicated formative study that preceded and informed the clinical objectives described in this protocol.

This formative work engaged patients with KS, healthcare providers, and community representatives in refining the SS3D device and usage protocols prior to clinical evaluation.

The formative study used a sequential mixed-methods approach comprising three components. First, focus group discussions (FGDs) were conducted with three stakeholder groups (patients with KS, end-users such as oncologists, dermatologists, clinical officers, and nurses, and community representatives from patient advocacy groups) in both Kenya and Uganda. In-depth interviews (IDIs) were conducted with up to 15 additional community stakeholders including community advisory board members, patient advocates, caregivers, and medical regulatory authorities. These qualitative activities were designed to understand current perspectives on KS skin lesion assessment, identify barriers and facilitators to adopting new technologies, and assess local cultural sensitivities and preferences that may influence acceptability and adoption of SS3D.

Second, findings from the FGDs and IDIs informed the development of a discrete choice experiment (DCE) survey that quantified end-user preferences for various design features of SS3D (e.g., camera resolution, data processing time, accessibility, ease of use, language support).

Third, iterative human-centered design (HCD) workshops were conducted using the Discover, Design/Build, and Test (DDBT) framework. These co-creation workshops brought together previous FGD and DCE participants, research team members, and technology experts for structured prototyping sessions. Participants were trained on SS3D use and asked to verbalize their experiences using a think-aloud protocol. Design activities yielded visualized outputs (drawings, pictures, paper prototypes, participant-written insight statements) and ethnographic field notes. Results were submitted to the manufacturer (Pensievision) for device redesign of hardware, software, and user guides, while local research teams refined standard operating procedures.

From this formative work, we synthesized findings and developed a refined SkinScan3D package with optimized hardware, software, and SOPs, while maintaining already present specific desirable attributes (operation without electricity or internet, no moving parts for durability, internal self-checks, self-calibration). The outputs of this formative work directly shape the SS3D intervention package evaluated in the clinical objectives of this protocol.

### Trial design {12}

PRIME-KS uses a two-objective sequential design within an exploratory framework. Objective 1 is a cross-sectional diagnostic reproducibility and accuracy study comparing SS3D with ruler-based KS lesion measurement. It uses a paired design in which two clinicians independently measure three lesions per participant using both methods. Objective 2 is a non-randomized before-and-after pilot study in which providers first use the manual ruler-based method for three months, then switch to using SS3D, allowing within-provider comparison of implementation outcomes. There is no randomization; the study is a prospective single-arm observational study to validate accuracy, reproducibility, and clinical workflow integration.

## Methods: Participants, interventions and outcomes

### Trial setting {13}

The Kenya sites are Homa Bay County Referral Hospital and the Kenya Medical Research Institute (KEMRI) located within the Jaramogi Oginga Odinga Teaching and Referral Hospital (JOOTRH) compound in Kisumu, Kenya. JOOTRH is the largest cancer treatment center and tertiary referral hospital in western Kenya, serving a population of over 10 million people.

KEMRI houses the NIH Division of AIDS Clinical Trial Unit and has hosted major KS treatment trials including AMC 066/ACTG A5263. Uganda site activities will be implemented at the Infectious Diseases Institute (IDI) HIV clinic and the Uganda Cancer Institute (UCI) located within the Mulago Hospital Complex in Kampala, Uganda. UCI has been the national cancer treatment, research, and teaching center since 1967 and has hosted multiple KS studies. IDI provides coordination support and patient referral for KS diagnosis.

### Characteristics of the people who are needed for the trial

This study will enroll all adults aged 18 years or older diagnosed and treated for KS who consent to participate in Kenya and Uganda. Objective 1 will include adult patients with a confirmed diagnosis of KS eligible for chemotherapy. In Objective 2, we will include both adult patients with KS undergoing treatment, providers (oncologists, medical officers, and nurses), and administrators involved in delivering KS treatment.

### Eligibility criteria for participants {14a}

#### Objective 1 (Reproducibility and Accuracy)

##### Inclusion criteria:

Age 18 years or older; histopathology-based KS diagnosis; at least three discrete skin lesions; capable of informed consent; on treatment for KS (chemotherapy and/or antiretroviral therapy).

##### Exclusion criteria:

Patients not initiating KS treatment or very ill and requiring hospitalization.

#### Objective 2 (Clinical Validation)

##### Patient inclusion criteria:

Histopathology-based KS diagnosis; at least three discrete skin lesions; age 18 years or older; capable of informed consent; initiating treatment for KS (chemotherapy and/or antiretroviral therapy).

##### Patient exclusion criteria:

Patients, not willing to participate.

##### Provider and administrator inclusion criteria:

Oncologists, medical officers, nurses, and administrators involved in delivering KS treatment at a participating site.

### Eligibility criteria for sites and those delivering interventions {14b}

The pre-selected participating sites are health facilities that provide routine KS treatment services in Kenya and Uganda, with institutional support for study implementation and capacity for ethical review and regulatory compliance. Clinicians delivering the SS3D intervention at each site will complete a structured training program that includes didactic instruction on the ACTG measurement criteria and practical sessions on SS3D device operation and the standardized measurement protocol.

### Who will take informed consent? {32a}

Informed consent from potential trial participants will be obtained by trained research assistants. Study staff will provide potential study participants with sufficient information about the study, details of the data collection component they will participate in, and their role in the study. This includes a brief video describing the device and its function that will be shared with participants during the consenting process. All consent forms will be translated into the local languages (Kiswahili, Dholuo, Luganda) and back-translated into English to ensure correct use of language. Health facility and study staff will be on hand to answer any questions that arise before signing the form. We anticipate that a minority of eligible patients may not be able to read or write. In this case, study staff will read the consent document to the eligible participant who will then be asked to place a thumbprint on the signature line. Reading and signing of consent documents will be witnessed and the witness will sign the informed consent form.

### Additional consent provisions for collection and use of participant data and biological specimens {32b}

No biological specimens are collected in this study. The informed consent form includes provisions for the collection and storage of de-identified imaging data (3D images of skin lesions) for the purposes of device calibration, algorithm improvement, and future research. Participants may decline permission for future use of imaging data while still participating in the study. If future scientific aims require biological specimens, the study protocol will be amended in line with institutional ethical review procedures at each site.

### Intervention and comparator

#### Intervention and comparator description {15a}

##### Intervention (SkinScan3D):

SS3D is a portable, handheld 3D imaging device manufactured by Pensievision. It uses a photon recording device combined with active optics capable of rapid change of focus, thereby achieving one-click, all-focus, 3D imaging using only a single perspective. The device consists of a custom-designed light ring (enabling white- and colored-light imaging), an electronically controlled liquid lens (Corning Varioptic A-16F0), an 8-megapixel camera, and a Raspberry Pi 4 Model B microcomputer with a 6-inch touchscreen display, all housed in a polycarbonate enclosure. A cup-shaped front-end adaptor ensures fixed shooting angle, camera-to-skin distance, and controlled illumination. A 73-frame image set requiring 8-9 seconds to collect is processed by AI software to generate a 3D map. The device provides automated measurements of lesion area, height, volume, and color. It operates on an internal lithium battery without requiring electricity or internet connectivity. The disposable front-end adaptor is the only consumable component. For each participant, five 3D snapshots of each of three target lesions are collected.

##### Comparator (ruler-based measurement):

Participants will have three discrete skin lesions measured using the standard ACTG method, in which lesion area is determined as the product of the longest perpendicular diameters using a ruler with millimeter precision (Figure 1).^1, 2^ This is the current global standard for KS response assessment in clinical trials.

#### Criteria for discontinuing or modifying allocated intervention/comparator {15b}

There are no anticipated criteria for modifying the allocated measurement method during the study. Participants may withdraw from the study at any time.

#### Strategies to improve adherence to intervention/comparator {15c}

All clinicians will receive structured training on both measurement methods prior to data collection, including didactic instruction and supervised practice sessions. A standardized measurement protocol and clinical checklist will guide device operations at each encounter. The SS3D software includes built-in self-checks that alert the user to hardware errors and data quality issues. Regular site monitoring visits and study team meetings will reinforce protocol adherence.

#### Concomitant care permitted or prohibited during the trial {15d}

All participants will continue to receive their standard KS treatment (chemotherapy and/or antiretroviral therapy) as directed by their treating clinicians. The study does not modify or restrict any aspect of clinical care. SS3D measurements are performed in addition to, not instead of, standard clinical assessments during the study period.

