##### Secondary outcomes:

(1) Acceptability of Intervention Measure (AIM), Intervention Appropriateness Measure (IAM), and Feasibility of Intervention Measure (FIM) scores.^12^ (2) Time-and-motion data characterizing clinic workflows, task-shifting, and time associated with clinic visits. (3) Implementation cost per patient and per visit, estimated using activity-based micro-costing.^13^

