### Participant timeline {18}

#### Objective 1

Each participant will complete a single study visit. At this visit, written informed consent will be obtained, demographic and clinical data collected, and three marker lesions identified. Two clinicians will independently measure the three lesions using both the ruler-based method and SS3D. The total additional time for study procedures is estimated at 15 to 30 minutes beyond the routine clinic visit.

#### Objective 2

During months 1 to 3 (control period), providers will measure KS lesions using the standard ruler-based method. Providers will also complete training on SS3D during this period. Thereafter, self-administered survey questionnaires will be used to gather information on usability, acceptability, appropriateness, and feasibility of the SS3D intervention. During the intervention period, providers will switch to using SS3D for KS lesion measurements. Time-and-motion observations and cost data collection will occur throughout both periods. Semi-structured interviews with a purposive sample of providers will then be conducted after the intervention period.

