### Who will be included in each analysis {27b}

All enrolled patients with complete paired measurements will be included. Analysis for Objective 1 will be at the lesion level (up to 150 lesions from 50 participants). For Objective 2, the usability and implementation outcome analyses will include all providers who completed the relevant questionnaires. The cost analysis will include all patients enrolled during the study period.

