### How missing data will be handled in the analysis {27c}

For Objective 1, if a measurement cannot be completed for a particular lesion using one method (e.g., SS3D cannot image a lesion on a highly curved surface), that lesion will be excluded from the paired analysis for that method. We will report the proportion and reasons for missing measurements. Given the cross-sectional, single-visit design, we anticipate minimal missing data. No imputation is planned for Objective 1. For Objective 2, if a provider does not complete a questionnaire, available data will be analyzed and the extent of missing data reported. For the cost analysis, missing cost elements will be estimated using median values from the available data at the same site.

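### Objective 2 says two ways whether the ruler continues once SS3D is in use, so its time comparison has no fixed meaning; separately, a site-median fill does not suit a total or per-patient cost

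*Protocol article*

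**What the plan says.** All references are to the protocol article.

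On the measurement method in Objective 2:

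- Trial design {12}: "providers first use the manual ruler-based method for three months, then switch to using SS3D". The same sentence says that this permits a comparison within providers.
- Participant timeline {18}: "During the intervention period, providers will switch to using SS3D for KS lesion measurements". On data capture it adds: "Time-and-motion observations and cost data collection will occur throughout both periods".
- Concomitant care {15d}: "SS3D measurements are performed in addition to, not instead of, standard clinical assessments during the study period". This sentence is not limited to Objective 1.
- Choice of comparator {9b}: "The comparator is the current standard of care for KS lesion measurement: manual ruler-based assessment using ACTG criteria". The Objective 2 measurements section under {25a} also treats the ruler phase as usual standard of care.

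On the outcomes and the cost rules:

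- One secondary outcome of Objective 2 is "Time-and-motion data characterizing clinic workflows, task-shifting, and time associated with clinic visits"; another is implementation cost per patient and per visit.
- Statistical methods {27a} plans an overall SS3D programme cost per patient and per visit, leaving out research costs, broken down by the categories in Table 2.
- Analysis sets {27b}: "The cost analysis will include all patients enrolled during the study period".
- Missing data {27c}: "missing cost elements will be estimated using median values from the available data at the same site".

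**The concern.** Read literally, the ruler both stops and continues in the SS3D period. Sections {12} and {18} describe replacement. Section {15d} describes addition to standard assessment, and {9b} says that standard assessment of lesions is the ruler. Two sites following different sections could run different after-periods, and the time-and-motion data would then measure different things. The Discussion hopes that SS3D will lighten providers' workload, and these are the data that would bear on it.

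The cost rule raises a separate question. A total or a mean cost is recovered by filling gaps with a mean. A median fill falls short of it whenever the element is right-skewed, as patient expenses and observed staff time often are.

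**Working it through.** The protocol gives no time, cost or missing-data figure for Objective 2, so there is no stated result to reproduce. Figures marked as assumed below are illustrations.

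**1. Replacement against addition.** Let R be ruler time and S be SS3D time per visit.

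- Before-period measurement time: R.
- After-period time if SS3D replaces the ruler: S, so the change is S − R.
- After-period time if SS3D is added: R + S, so the change is (R + S) − R = S.
- The two readings differ by exactly R. Because S is positive, the change under addition is always an increase.

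For the size of S, {15a} gives 8 to 9 seconds per image set, and five snapshots of each of three lesions per participant:

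- 3 × 5 × 8 = 120 s and 3 × 5 × 9 = 135 s, that is 2.0 to 2.25 min.
- This is image capture only. The Objective 2 measurements section does not repeat the snapshot count.

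| R (assumed) | S (assumed) | Change if replaced (S − R) | Change if added (S) |
|---|---|---|---|
| 5 min | 2.25 min | −2.75 min | +2.25 min |
| 20 min | 2.25 min | −17.75 min | +2.25 min |
| 10 min | 5 min | −5 min | +5 min |
| 5 min | 10 min | +5 min | +10 min |

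The sign reverses whenever R exceeds S. When S exceeds R, only the size changes.

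**2. Median fill.** Suppose a share m of one cost element is missing and is filled with the median. The relative error in that element's mean is m × (median/mean − 1). For a lognormal element with log-SD s, median/mean = exp(−s²/2).

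- s = 0.8: exp(−0.32) = 0.726, so the median is 27% below the mean.
- s = 1.0: exp(−0.5) = 0.607, so the median is 39% below the mean.
- m = 10%, s = 0.8: 0.10 × 0.274 = 2.7% understated.
- m = 30%, s = 1.0: 0.30 × 0.393 = 11.8% understated.

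The same calculation by coefficient of variation (CV), where median/mean = 1/√(1 + CV²), for 5% to 30% missing:

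- CV 0.5: 0.5% to 3.2% understated.
- CV 1.0: 1.5% to 8.8% understated.
- CV 1.5: 2.2% to 13.4% understated.

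The error is zero if the element is symmetric or complete. If the element makes up a share w of total cost, the total is understated by w times these figures.

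**3. Denominator.** If a share f of the counted patients never had SS3D, an SS3D cost per patient is multiplied by 1 − f. The sample size section {19} rolls SS3D out to 100 participants. If all of them receive it, f = 0 and nothing changes.

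**The case against.** The milder reading of {15d} deserves weight. The sentence sits under concomitant care and speaks of clinical assessments, not of the ruler. The Introduction says that the ACTG method is impractical in routine care and that clinicians rely mainly on subjective observation. Continuing that kind of assessment is compatible with changing the measurement method. This makes the text ambiguous and does not prove that the ruler continues. But no section states the milder reading, and {9b} and {25a} point the other way, so a reconciling sentence is still needed.

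The removal of research costs in {27a} could also take out a ruler measurement repeated only for the study. That helps the cost outcome in part. A ruler measurement classed as standard care would not clearly be removed, and no such exclusion is stated for time-and-motion data.

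Four stronger inferences are tempting, and the documents do not support them:

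- **That costs are imputed with a median over all enrolled patients.** {27c} fills only missing elements, from the same site. {27b} separately defines the analysis set.
- **That time and cost will be biased in a known direction.** A retained ruler raises time and cost, while a median fill lowers cost. Whether either occurs depends on facts that are not stated. The cost outcome is also planned as a level for SS3D and not as a difference from the ruler, so no cost contrast can be reversed.
- **That total cost is understated by 3 to 12%.** Most Table 2 categories rest on expense reports, salary scales or manufacturing and shipping costs. The skew argument fits mainly patient costs and observed staff time.
- **That ruler-only patients dilute the cost per patient.** Given {19}, this is hypothetical. What remains is that {27b} does not say which visits count, although cost data are collected in both periods.

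Finally, the Discussion describes Objective 2 as characterising implementation and admits temporal confounding. That limits how much rests on the time contrast, but does not settle what it measures.

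**Conclusion.** The contradiction between {12} and {18} on one side and {15d} on the other stands. It changes the before-after time outcome by the whole ruler time R, and can reverse its sign when R exceeds S. Personnel cost may be affected too, unless the ruler time is removed as a research cost.

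The median fill is a smaller, independent flaw: about 3 to 12% of an affected element under the assumed skew and missingness, less of the total, and nothing for symmetric or complete elements. The denominator needs only a clarifying sentence.

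All of this concerns secondary outcomes of an exploratory pilot. The System Usability Scale (SUS) primary outcome is untouched.

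**What to change.** - Reconcile {12}, {15d} and {18} on whether ruler measurement continues in the SS3D period. Which of the two holds is for the investigators to state.
- Whichever holds, record ruler time and SS3D time separately at each observed visit, and base the time and personnel-cost outcomes on the method-specific component.
- In {27c}, replace the site median with the site mean or multiple imputation, within study period where an element differs between periods.
- In {27b}, state that SS3D cost per patient and per visit counts only patients and visits with SS3D.

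The cost is some rewording and slightly more recording at observed visits. Cost per patient may come out slightly less favourable, and a mean is more sensitive to outliers than a median. The change is best made now: the trial status section says that Uganda began recruiting on 1 April 2026 and Kenya has not begun, and method-specific times that were not recorded cannot be recovered later.
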